## Abstract

**Background:**

An estimated 285 million people worldwide have diabetes and its prevalence is predicted to increase to 439 million by 2030. For the year 2010, it is estimated that 3.96 million excess deaths in the age group 20-79 years are attributable to diabetes around the world. Self-management is recognised as an integral part of diabetes care. This paper describes the protocol of a randomised controlled trial of an automated interactive telephone system aiming to improve the uptake and maintenance of essential diabetes self-management behaviours.

**Methods/Design:**

A total of 340 individuals with type 2 diabetes will be randomised, either to the routine care arm, or to the intervention arm in which participants receive the Telephone-Linked Care (TLC) Diabetes program in addition to their routine care. The intervention requires the participants to telephone the TLC Diabetes phone system weekly for 6 months. They receive the study handbook and a glucose meter linked to a data uploading device. The TLC system consists of a computer with software designed to provide monitoring, tailored feedback and education on key aspects of diabetes self-management, based on answers voiced or entered during the current or previous conversations. Data collection is conducted at baseline (Time 1), 6-month follow-up (Time 2), and 12-month follow-up (Time 3). The primary outcomes are glycaemic control (HbA1c) and quality of life (Short Form-36 Health Survey version 2). Secondary outcomes include anthropometric measures, blood pressure, blood lipid profile, psychosocial measures as well as measures of diet, physical activity, blood glucose monitoring, foot care and medication taking. Information on utilisation of healthcare services including hospital admissions, medication use and costs is collected. An economic evaluation is also planned.

**Discussion:**

Outcomes will provide evidence concerning the efficacy of a telephone-linked care intervention for self-management of diabetes. Furthermore, the study will provide insight into the potential for more widespread uptake of automated telehealth interventions, globally.

**Trial Registration Number:**

ACTRN12607000594426

## Background

Diabetes is a leading cause of death and morbidity and is a health priority in Australia and worldwide. Over 285 million people have diabetes around the world [1] (90% of whom are diagnosed with type 2 diabetes). For the year 2010, it is estimated that 3.96 million excess deaths in the age group 20-79 years are attributable to diabetes around the world [2]. The number of people living with diabetes is predicted to reach 439 million in 2030 [1]. Poor glycaemic control, as measured by Haemoglobin A1c (HbA1c), significantly increases one's risk of costly diabetes-related complications [3,4].

Self-management is an integral component of effective diabetes care [5]. Systematic reviews of interventions targeting diabetes self-management indicate that the effectiveness of these programs is significantly related to their duration [6,7]. This emphasises the importance of ongoing follow-up and support for successful long-term glycaemic control [8].

The delivery of ongoing support to the fast growing number of people living with diabetes presents a real challenge for most health systems and this will not be addressed by any modest increase in the number of relevant health professionals to provide such services. Addressing this challenge requires new cost-effective approaches that will reach a large number of individuals regularly, in particular, those people who already have poor access to current services, due to geographical, financial or other barriers.

Programs using automated information and telecommunication technologies offer a potential solution to chronic disease management as they can be conveniently accessed from home or office and at any time of the day or night. Reviews of such interactive automated technologies in chronic disease care, including diabetes [9-11], report positive effects on users' self-care knowledge, clinical and behavioural outcomes, social support and health care utilisation. In addition, acceptability of automated telephone programs among users has been shown to be high [12]. Further, the logical structure, on which computerised interventions are built, means that they offer a consistency of delivery which is difficult to achieve in programs delivered by health professionals. Therefore, these technologies hold promise as a new approach to overcome barriers associated with the traditional delivery of chronic disease self-management programs by offering effectiveness, accessibility and consistency. They may also prove to be cost-effective.

The use of a telephone as the mode of access to these programs makes them available to the majority of the population. The Telephone-Linked Care (TLC) system is an interactive computer assisted telephone system which has been shown to improve health behaviours and to be acceptable to users [13-17]. This system consists of a computer connected to the telephone network, equipped with speech recognition, numerous pre-recorded conversation statements and a database in which users' answers are stored. It is designed to emulate telephone conversations between patients and health professionals. It tailors its responses, including feedback and encouragement, according to data entered in the TLC database and the answers that it receives during the current and previous calls.

This paper presents the study protocol for a randomised controlled trial (RCT) of a TLC system aiming to improve type 2 diabetes management, TLC Diabetes. We hypothesise that participants in the intervention arm will demonstrate greater improvements in HbA1c and health-related quality of life (QoL) compared to those in the control arm. Secondly, we hypothesise that the intervention will be cost-effective compared with the control arm. The results of this study will provide valuable information about the efficacy, cost-effectiveness, acceptability and feasibility of a novel way to improve type 2 diabetes self-management.

## Methods/design

### Study design

The study is a two-arm prospective RCT in which a total of 340 adults with type 2 diabetes will be randomised to either the intervention (TLC Diabetes program) or 'routine care' control arm. Participants in both arms complete assessments at baseline (Time 1), 6-month follow-up (Time 2), and 12-month follow-up (Time 3).

### Study aims

*Primary Aim*: To investigate the effects of the TLC Diabetes program on health outcomes (primary outcome variables include HbA1c and QoL measured using the Short Form-36 version 2 [SF-36v2]) post intervention (Time 2) and at 12- month follow-up (Time 3).

*Secondary Aim*: To examine the cost-effectiveness of the intervention arm in comparison with the control arm.

### Study sample

#### Eligibility criteria

Eligibility criteria include: a type 2 diabetes diagnosis of at least 3 months; aged 18 - 70 years; residing in the greater Brisbane area (Australia); an HbA1c level of at least 7.5%; stable diabetes pharmacotherapy type for at least 3 months; stable pharmacotherapy dosage for at least 4 weeks; ability to clearly speak and understand English via the telephone, and weekly access to a telephone. Participants are excluded if they are: diagnosed with a condition with likely poor prognosis within 1 year; diagnosed with dementia or a psychiatric co-morbidity; pregnant, lactating, or planning to become pregnant within the next 12 months; currently enrolled in another intervention trial; or have undergone bariatric surgery in the past 2 years.

#### Sample recruitment procedures

A range of recruitment strategies are used including advertisements in newspapers and community newsletters and distribution of flyers to a large number of health professionals to provide to patients diagnosed with type 2 diabetes. Patients of diabetes clinics of three major hospitals in Brisbane and clients of Diabetes Australia - Queensland's shops and information seminars are also informed of the study by research staff or by flyers placed in reception areas.

Individuals expressing interest in participating are screened in two stages. They are firstly assessed against eligibility criteria at first contact via telephone or in person. If deemed potentially eligible, they attend a baseline appointment at one of two large teaching hospitals, the Princess Alexandra Hospital (PAH) or the Royal Brisbane and Women's Hospital (RBWH) in Brisbane, where they are provided with a comprehensive explanatory statement. After signing the study consent form, they complete the baseline questionnaires and a hospital phlebotomist takes the blood specimens required. They are excluded if the HbA1c result from this blood test does not meet the HbA1c criterion.

#### Sample size calculations

A total of 340 eligible participants will be recruited to the study. It is anticipated that there will be an attrition rate of up to 30% over the 12 months of follow-up, so we expect complete data on 238 participants. With 238 completing participants, we shall be able to detect, with 90% power and type I error of 5% (two-tailed), excess intervention effects over routine care effects of at least 0.4% (from baseline 8.9% to 8.5%) in HbA1c. The calculations for HbA1c were based on standard deviations of change of 1% in both groups, conservatively estimated assuming maximum physiological range of 3% improvement or deterioration of individuals. An effect size of 0.4% in our primary outcome, HbA1c, was chosen for our sample size calculations as per Toobert [18], who calculated that a change of 0.4% translates into a clinically meaningful 14% reduction in risk of diabetes complications based on the analysis of the UK Prospective Diabetes Study in patients with type 2 diabetes. For SF-36v2 physical and mental component summary scores, a sample of 238 completed participants has 90% power to detect a difference of 3.9 units (assuming standard deviation of 10 [19]).

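### On the plan's own inputs, 238 completers give about 87% power for 0.4% HbA1c and about 85% for 3.9 SF-36v2 units, not the stated 90%

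*Protocol article*

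**What the plan says.** The Sample size calculations section of the protocol article makes these statements:

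- Recruitment and attrition: "A total of 340 eligible participants will be recruited to the study", with "attrition rate of up to 30% over the 12 months of follow-up, so we expect complete data on 238 participants".
- HbA1c: "With 238 completing participants, we shall be able to detect, with 90% power and type I error of 5% (two-tailed), excess intervention effects", the effect being "excess intervention effects over routine care effects of at least 0.4% (from baseline 8.9% to 8.5%) in HbA1c". The SD of change is taken as 1% in each arm. The 0.4% is described as a chosen effect size, justified by its clinical meaning.
- SF-36v2 physical and mental component summaries: "a sample of 238 completed participants has 90% power to detect a difference of 3.9 units (assuming standard deviation of 10".

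No correlation between baseline and follow-up appears in the section. The Data analyses section separately plans an ANCOVA with the baseline score as covariate. HbA1c and SF-36v2 are the two primary outcomes (Study aims; Table 1).

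**The concern.** Every input to a two-group comparison of means is printed, so the 90% can be checked directly, and it looked too high for both outcomes. The two statements also sit awkwardly together. At the same sample size and power, one implies a detectable effect of 0.40 SD and the other 0.39 SD.

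These are the only design figures given for the two primary outcomes. If they are too favourable, the chance of missing the stated effects is larger than readers are told. A non-significant result could then be read as stronger evidence against effects of 0.4% and 3.9 units than the design supports. The apparent tolerance for 30% attrition would also be overstated.

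**Working it through.** **Inputs** (Sample size calculations section, except allocation)

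- Completers: 340 × 0.70 = 238. This step is correct.
- Allocation: no numerical ratio is given. Two arms with blocked randomisation (Study integrity) suggest 1:1, so 119 per arm. Unequal allocation would lower power further.
- Two-sided α = 0.05, so z = 1.960. For 90% power, z = 1.2816. Sum = 3.2415.
- HbA1c: difference 0.4, SD of change 1. SF-36v2: difference 3.9, SD 10.

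**Trying to reproduce the stated 90%**

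Power = Φ(δ/SE − 1.960), with SE = SD × √(2/n) and √(2/119) = 0.1296.

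| Outcome | SE | δ/SE | Power (normal) | Power (t-test) |
|---|---|---|---|---|
| HbA1c, 0.4% | 0.1296 | 3.085 | Φ(1.125) = 87.0% | 86.7% |
| SF-36v2, 3.9 units | 1.296 | 3.008 | Φ(1.048) = 85.3% | 85.0% |

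The 90% is not reproduced for either outcome. Type II error is about 13% and 15%, against the implied 10%.

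**Difference detectable with 90% power**

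3.2415 × 0.1296 = 0.420 SD, that is 0.42% HbA1c and 4.2 SF-36v2 units.

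**Completers needed for 90% power**

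n per arm = 2 × 3.2415² / (δ/SD)².

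- HbA1c: 2 × 10.507 / 0.16 = 131.3, so 132 per arm, 264 in total (t-test: 133 and 266).
- SF-36v2: 2 × 10.507 / 0.1521 = 138.2, so 139 per arm, 278 in total (t-test: 140 and 280).

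From 340 recruited, this allows attrition of 1 − 264/340 = 22% for HbA1c and 1 − 278/340 = 18% for SF-36v2. At 30% attrition, recruitment would have to be 378 and 398.

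**Other readings tried**

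- One-sided 5%: 92.5% and 91.4%, but the section says two-tailed.
- All 340 analysed: 95.8% and 94.9%, but the claim is made for 238.
- 85% power, two-sided: (1.960 + 1.036) × 0.1296 = 0.388 SD, which prints as 3.9 units and, to one decimal, 0.4%. Both printed differences therefore fit 85% power. That this is how the error arose is only a guess.

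**What ANCOVA would need**

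For 90% power the residual SD must fall to 0.4/0.420 = 0.952 for HbA1c and 3.9/0.420 = 9.28 for SF-36v2. Let ρ be the baseline to follow-up correlation, with equal variances at the two visits.

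- HbA1c, SD of change 1: the residual SD is √((1+ρ)/2), so ρ must be no more than 2 × 0.952² − 1 = 0.81 (t-test about 0.80).
- SF-36v2, reading 10 as the SD of the score: the residual SD is 10√(1−ρ²), so ρ must be at least √(1 − 0.928²) = 0.37 (t-test about 0.38).
- The section does not say whether 10 is the SD of the score or of its change. If of change, the condition becomes ρ of no more than 2 × 0.928² − 1 = 0.72.

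**The case against.** The best defence is that the calculation above is not the planned analysis. The Data analyses section specifies ANCOVA, and over a wide range of correlations that model gives 90% or more. With t-test power and 10 read as the SD of the score, ρ = 0.5 gives 94.4% for HbA1c and 93.3% for SF-36v2. A condensed article may also leave out the correlation. This part stands: true power may well reach 90%. It does not rescue the printed claim, because the HbA1c calculation is said to rest on the SD of change, which is an unadjusted comparison, and nothing in the section invokes baseline adjustment.

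Second, 0.42% rounds to 0.4%, and the SD of 1% is called conservative. For HbA1c this softens the point but does not remove it, since 0.4% is presented as a chosen effect size and not as a rounded detectable difference. For SF-36v2 rounding is no answer: 4.2 is not 3.9.

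Third, the 0.40 against 0.39 mismatch may itself be rounding, because HbA1c is given to one decimal. That is fair, and it is a supporting observation only.

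Fourth, results will be reported with 95% confidence intervals, attrition of 30% is an upper bound, and a generalised estimating equations analysis will use partial data. These limit the practical harm; they do not make the power statement correct.

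**Conclusion.** The concern holds. On the section's own inputs, 238 completers give about 87% power for 0.4% HbA1c and about 85% for 3.9 SF-36v2 units. The differences detectable with 90% power are 0.42% and 4.2 units.

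The conclusion assumes 1:1 allocation and an unadjusted two-sided comparison with the printed SDs. It concerns what those inputs support and does not show that the ANCOVA will fall short of 90%.

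The shortfall of 3 to 5 percentage points is moderate and does not threaten the design. It should still be corrected, because the figure is wrong as stated for both primary outcomes; the SF-36v2 figure is the clearer error.

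**What to change.** Keep 340 participants and take one of two routes.

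1. **Restate the power.** For example: *238 completers give 87% power to detect a 0.4% difference in HbA1c and 85% power to detect 3.9 SF-36v2 units (two-sided 5%, unadjusted); with 90% power the detectable differences are 0.42% and 4.2 units.*
2. **Recompute for the planned ANCOVA.** State the assumed baseline to follow-up correlation for each outcome with its justification, and say whether the SF-36v2 SD of 10 is for the score or its change. The 90% claim then stands only if the correlation is no more than about 0.80 for HbA1c and, with 10 as the SD of the score, at least about 0.38 for SF-36v2.

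Either route changes wording only. The first makes the stated power slightly less favourable; neither adds participants or alters an outcome or analysis.

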### Ethics approval

Ethics approval was received from Human Research Ethics Committees of the Princess Alexandra Hospital (No. **2007/029**), Royal Brisbane and Women's Hospital (No. **HREC/09/QRBW/21**), Prince Charles Hospital (No. **HREC/O9/QPC HJ26**), the University of Queensland (No. **2007000899**) and Monash University (No. **CF07/0313 - 2007/0102**).

### Study arms

All participants receive a quarterly newsletter consisting of general health information; this aims to maintain participation.

#### Control arm

Control participants are advised to continue their routine medical care.

#### Intervention arm

Intervention participants also continue their routine medical care. In addition, they receive the TLC Diabetes program which was developed collaboratively between the Australian research team and USA researchers at the Medical Information Systems Unit, Boston University [20,21]. The TLC Coordinator, whose role is to support intervention group participants in all aspects of use of the TLC Diabetes program, meets with participants within one week of their Time 1 data collection to provide them with the TLC Diabetes kit containing the TLC Handbook, an *ACCU-CHEK*^® ^*Advantage *glucose meter, test strips, and a Bluetooth™ device with which to upload their blood glucose results to the TLC Diabetes system. The TLC Handbook contains instructions and general information on the TLC Diabetes program, a number of Diabetes Australia diabetes management fact sheets plus sheets on which to record notes and information related to the program. A quit smoking information pack, containing a self-help booklet and brochures, is also provided to current smokers. During this meeting, participants also receive instructions on how to operate the glucose meter and the uploading Bluetooth™ device and complete a training call to the TLC Diabetes system. Participants are asked to perform all blood glucose self-monitoring with the study glucose meter and to upload its readings immediately preceding their weekly telephone conversations with the TLC system.

Participants choose a unique personal password which they enter at the start of each call to the system and which is linked to their database file and ensures correct subject identification and confidentiality. Prior to the participants' first call to the system the TLC Coordinator obtains personalised self-care clinical targets for the participants from their primary health care provider. This includes recommended number of daily blood glucose tests, ideal fasting blood glucose range and clearance for physical activity. Once this information is entered into the database, participants start making weekly calls to the system over a period of 24 weeks. The calls are at no cost to them and they can last between 5 and 20 minutes (depending upon the content of the call and the participant's responses). Blood glucose monitoring is the first topic covered in each weekly call. It is followed by one of the following topics: medication-taking (calls 1-4; 13-16), physical activity (calls 5-8; 17-20), and healthy eating (calls 9-12; 21-24). When a participant does not take any medication prescribed for diabetes, the medication-taking topic is replaced by physical activity. When the treating physician does not provide clearance for physical activity, this topic is replaced by medication-taking. In cases when there is no clearance for physical activity and no pharmaceutical treatment of diabetes, the participant does not hear a second topic on calls 1-8, and 13-20.

The TLC Coordinator phones participants after their first two calls to the TLC system and at weeks 6, 12 and 20, to identify and resolve any issues faced during their use of the TLC Diabetes system or to identify reasons for not calling regularly. Additionally, the TLC Diabetes system sends email "alerts" to a dedicated project email address to signal the need for the Coordinator to contact a participant regarding technical or other issues.

### Study integrity

The study design is according to the recommendations of the CONSORT statement for randomised trials of non-pharmacologic treatment [22]. Randomisation to an experimental group occurs after the Time 1 baseline assessment is completed. Arm allocation is conducted using a 4 × 4 block randomised block design with the participant as the unit of randomisation. Due to the complex nature of the intervention, it is not possible to blind research staff to group allocation. The intervention protocol is documented and the data generated during the calls made by participants is stored in the TLC database. All analyses will be conducted based on the principle of intention to treat.

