### Measurement

All assessments (Table 1) are administered at the PAH or RBWH but at the same location for Time 1, 2 and 3. Blood specimens are collected according to Queensland Health guidelines. Waist and hip circumferences are measured according to WHO MONICA guidelines [23]. Behaviour, psychosocial and health care utilisation (HCU) questionnaires are self-administered.

**Table 1 T1:** Primary and secondary outcome measures for times 1, 2 and 3

Variable	Instrument

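### The one block scheme stated, apparently blocks of 4, could make up to a third of allocations certain in advance if unblinded recruiters see the sequence; undisclosed varying block sizes would be better

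*Protocol article*

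**What the plan says.** Study integrity describes the allocation in one sentence: "Arm allocation is conducted using a 4 × 4 block randomised block design with the participant as the unit of randomisation". Two statements in the same paragraph bear on it. One concerns blinding: "Due to the complex nature of the intervention, it is not possible to blind research staff to group allocation". The other concerns timing: "Randomisation to an experimental group occurs after the Time 1 baseline assessment is completed".

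Study design gives the arms and the size: "The study is a two-arm prospective RCT in which a total of 340 adults with type 2 diabetes will be randomised".

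Sample recruitment procedures shows that staff meet candidates before randomisation. Patients of three hospital clinics and clients of a diabetes organisation "are also informed of the study by research staff or by flyers placed in reception areas". Candidates are then screened by telephone or in person, and attend a baseline appointment at one of two hospitals. A laboratory check follows: "They are excluded if the HbA1c result from this blood test does not meet the HbA1c criterion". Under Measurement, each participant stays with one hospital: "All assessments (Table 1) are administered at the PAH or RBWH but at the same location for Time 1, 2 and 3".

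The article does not state the allocation ratio, whether the block size varies, or whether the list is split by hospital.

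**The concern.** In a permuted block of known size, anyone who has seen the earlier allocations can work out some of the later ones. The smaller the block, the more often this happens. Here a single scheme is printed in a public article, the natural reading is a block of 4, and the research staff are unblinded. Staff who could predict the next slot might, without intending it, approach or book a candidate sooner or later according to how motivated that person seems. They might also apply the eligibility criteria that need judgement differently, such as spoken English by telephone or likely prognosis.

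Motivation matters in this trial. The intervention is 24 weeks of calls that participants make themselves, SF-36v2 is one of the primary outcomes and is patient-reported, and attrition of up to 30% is expected. Analysis of covariance on the baseline score (Data analyses) does not fully remove selection on something that was not measured.

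The wording is a separate, smaller problem. For two arms, 4 × 4 does not tell the reader whether the block is 4, 16 or something else.

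**Working it through.** The article gives no predictability figure, so there is none to reproduce.

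**Inputs.** Two arms and 340 participants (Study design); a 4 × 4 block and unblinded staff (Study integrity); two hospitals (Measurement). **Assumed:** 1:1 allocation, fixed block size, and past allocations visible to the person guessing, except where stated.

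**Blocks of 4, whole sequence visible, certain assignments.** The fourth assignment is always determined. The third is determined when the first two match. The second matches the first with probability 1/3, because 1 of the 3 remaining places is in the same arm.

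- Per block: 1 + 1/3 = 4/3
- Share: (4/3)/4 = 1/3 = 33.3%
- Number: 340/3 = 113.3, about 113

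**Blocks of 4, best guess.** Guess the arm with more places left, and toss a coin when they are equal.

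- First: 1/2
- Second: 2/3
- Third: (1/3) × 1 + (2/3) × 1/2 = 2/3
- Fourth: 1
- Mean: (1/2 + 2/3 + 2/3 + 1)/4 = (17/6)/4 = 70.8%, against 50% by chance

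**Block of 16.** For block size 2m the certain share is 1/(m + 1). With m = 2 this gives 1/3, as above. With m = 8 it gives 1/9 = 11.1%, and 340/9 = 37.8, about 38 participants. Best-guess accuracy, by exact enumeration, is 62.8%.

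**Blocks of 4, one shared list, own hospital only.** Assume that each slot falls at either hospital with probability 1/2, and that staff see only their own hospital's allocations but know the position in the block.

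- Third slot: the first two match (1/3) and both were seen (1/4), giving 1/12.
- Fourth slot: among the first three, exactly two share an arm. The fourth is certain when both of those were seen, giving 1/4.
- Per block: 1/12 + 1/4 = 1/3. Share: (1/3)/4 = 1/12 = 8.3%, and 340/12 = 28.3, about 28 participants.

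**Randomly varying sizes.** These figures come from simulation (340 participants, 300 repetitions, sizes equally likely). The guesser is assumed to see the whole sequence and to know the set of sizes, but not the size of any one block.

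| Scheme | Certain in advance | Best guess correct |
|---|---|---|
| Fixed 4 (exact) | 33.3% | 70.8% |
| Mixed 4, 6 | 5.4% | 69.3% |
| Mixed 4, 8 | 7.5% | 68.0% |
| Mixed 4, 6, 8 | 2.1% | 68.1% |

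With sizes 4, 6 and 8, 0.021 × 340 is about 7 certain assignments instead of 113. The best guess improves by less than three percentage points (70.8 − 68.1 = 2.7).

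**The case against.** A reader might infer that staff know every allocation, that one third of assignments are therefore knowable, and that enrolment is biased. The article does not support that.

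- **Visibility.** The blinding statement says that research staff cannot be blinded to group. It does not say that those who recruit see or track the running sequence, or that they are the people who assign. This objection stands, so the one-third figure is conditional.
- **Block size and ratio.** Fixed and 1:1 are both inferred. Blocks of 4 is the natural reading, but wording that cannot be identified cannot also supply a firm 33%. This stands too, and is why the figures are given as a range.
- **Order of randomisation.** Assignment follows consent, questionnaires, blood sampling and an HbA1c result that may exclude the person. With several results pending, nobody can be sure who takes the next slot. This lowers predictability by an amount the article does not allow one to calculate. It does not remove it, because a prediction can be made before someone is approached or booked. The laboratory check also limits selection on HbA1c only, not on motivation.
- **Concealment detail.** Who generates and holds the list, and how allocations are released, is commonly left to the full protocol. Its absence from the article is not a fault, and the article already places randomisation after baseline.
- **Effect of the change.** Varying the block size hardly moves best-guess accuracy. This is correct, and it means that block size alone is not a sufficient remedy.

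What remains is the stated choice: one apparently small block scheme, made public, in a trial with unblinded staff who also have contact with candidates.

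**Conclusion.** The point holds in conditional form. If the scheme is 1:1 with blocks fixed at 4, and if recruiters can see past allocations, up to one third of assignments (about 113 of 340) are certain in advance and a best guess succeeds 70.8% of the time. One third is the upper end under the natural reading. The certain share is 11.1% (about 38) with a block of 16. It is 8.3% (about 28) with blocks of 4 on one list shared evenly between hospitals that see only their own allocations.

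Nothing in the article shows that selective enrolment has occurred, and no bias in HbA1c or SF-36v2 can be estimated from it. This is an inexpensive improvement to a stated design choice, plus a description that needs correcting under any reading.

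**What to change.** For participants still to be randomised, generate a new list with randomly varying block sizes, for example 4, 6 and 8, and do not disclose the sizes to recruiting staff. Replace the 4 × 4 wording with the scheme actually used: allocation ratio, permuted blocks, and the fact that sizes vary. The sizes themselves should stay in a restricted document until recruitment ends.

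This must go with allocation concealed from recruiters, because varying sizes remove most of the certainty but little of the guessing advantage. If the full protocol already provides for concealment, nothing more is needed on that score.

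Separate lists by hospital are not part of this fix. For a given block scheme they show local staff more of the sequence that matters to them. Under the assumptions above, blocks of 4 would give 33.3% certain on separate lists, against 8.3% on a shared one.

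The cost is a new list and an ethics amendment; the article lists five committees that gave approval. Arm sizes may also differ by a few participants. On one list, an incomplete last block of 8 can leave a difference of at most 4, plus up to 2 if a current block of 4 is abandoned part-way. That is small against 340.
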